**Methods:**

The study is a multicenter, single-blinded RCT with 10 years of follow-up. Overall, a minimum of 286 eyes (approximately 228 participants assuming 75% have two study eyes) will be recruited. This study will be carried out in four eye clinics across China. Consecutive eligible patients are randomized to undergo either secondary in-the-bag IOL implantation or secondary sulcus IOL implantation. Participants with two eyes eligible will receive the same treatment. The primary outcomes are IOL decentration and the incidence of glaucoma-related AEs. The secondary outcomes include the incidence of other AEs, IOL tilt, visual acuity, and ocular refractive power. Analysis of the primary and secondary outcomes is to be based on the intention-to-treat and per-protocol analysis. Statistical analyses will include the *χ*^2^ test or Fisher’s exact test for the primary outcome, mixed model and generalized estimated equation (GEE) model for the secondary outcome, Kaplan–Meier survival curves for the cumulative probability of glaucoma-related AEs over time in each group.

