### Sample size

According to the Zhongshan Ophthalmic Center’s outpatient record system, (1) the one-year incidence of glaucoma-related AEs in sulcus implantation is 12%. Assuming the in-the-bag implantation would reduce the absolute incidence to 0.7%, to achieve 90% power with a two-sided alpha of 0.0492 (the interim analysis at 6 months postoperatively spending alpha of 0.0054 by O’Brien-Fleming approach), 114 eyes are needed for each group (total of 228 eyes) using Fisher’s exact test with pooled variance. Allowing for a 20% loss to follow-up, 143 eyes should be needed in each group. Assumptions: % of bilateral = 75%, inter-eye correlation among bilateral patients = 0.5. For bilateral patients, two eyes have the same type of surgery. The number of patients (*X*) per group can be calculated by solving the following equation: *X* × 0.75 × 2/(1 + 0.5) + *X* × 0.25 = 143, *X* = 114 patients per group, a total of 228 patients. The sample size is calculated by PASS 16.0 (NCSS, LLC, USA). (2) IOL decentration in 3-dimension in the capsular group is 0.38 mm while in the sulcus group, it is 0.56 mm. Group sample sizes of 106 and 106 achieve 90% power to detect the mean difference of 0.18 between two trial arms with a common standard deviation for both groups of 0.40 and with a two-sided alpha of 0.0492 using a two-sided two-sample equal-variance *t*-test (same interim analysis as above for the 1-year incidence of glaucoma-related AEs). Allowing for a 20% loss to follow-up, 133 eyes should be needed in each group. Assumptions: % of bilateral = 75%, inter-eye correlation among bilateral patients = 0.5. For bilateral patients, two eyes have the same type of surgery. The number of patients (*X*) per group can be calculated by solving the following equation: *X* × 0.75 × 2/(1 + 0.5) + *X* × 0.25 = 133, *X* = 106 patients per group, a total of 212 patients. The sample size is calculated by PASS 16.0.

Considering the sample size calculated by the two primary outcomes, the largest one is selected: 114 patients per group, a total of 228 patients.

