### Statistical analysis

#### Statistical methods

The normality of continuous data is to be checked using the Shapiro–Wilk test and histogram. Continuous data are to be summarized as the mean ± standard deviation, median, or interquantile range (IQR). Analysis of the primary and secondary outcomes is to be based on the intention-to-treat (ITT) and per-protocol (PP) analyses, and missing data will be imputed by multiple imputation or other appropriate methods. In the ITT analysis, participants are evaluated on the basis of the group to which they were randomly assigned, regardless of whether they actually received the surgery. In the PP analysis, participants are evaluated on the basis of the group to which they actually received the surgery to truly reflect the difference between the two groups. Paired *t* test will be used to compare pre- vs. postoperative visual acuity (in logMAR), spherical equivalent aberration, IOL tilt, and decentration at each time point after surgery. Comparison between the two treatment groups will be performed using a mixed model for continuous outcomes and a generalized estimated equation (GEE) model for categorical outcomes. The incidence of glaucoma-related AEs (primary outcome) by 1 year will be compared using the *χ*^2^ test or Fisher’s exact test. Kaplan–Meier survival curves are to be constructed to show the cumulative probability of glaucoma-related AEs over time in each group, and the log-rank test is used to compare the time to incidence of glaucoma-related AEs between the two study groups. Unadjusted and adjusted hazard ratio (HR) of glaucoma-related AEs and 95% CIs will be estimated by univariable and multivariable Cox proportional hazards model, respectively. Study group, stratification variable (laterality), and other baseline variables with *P* < 0.20 in the univariable analysis will be included in the multivariable model. The inter-eye correlation will be adjusted for all analyses including both eyes from the same subject.

A two-sided *p* < 0.0054 for interim analysis and *p* < 0.0492 for the primary analysis is considered to be statistically significant. All statistical analysis will be performed using Stata 16 (StataCorp, College Station, TX, USA) and other appropriate software.

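### The tests named for the primary glaucoma outcome do not, in standard form, deliver the inter-eye adjustment that the same section promises

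*Protocol article*

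**What the plan says.** All references are to the protocol article.

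- **Statistical methods, primary test.** After giving mixed models to continuous outcomes and GEE to categorical ones, the section treats the glaucoma outcome separately: "The incidence of glaucoma-related AEs (primary outcome) by 1 year will be compared using the" chi-square test or Fisher's exact test.
- **Statistical methods, time course.** "the log-rank test is used to compare the time to incidence of glaucoma-related AEs between the two study groups". Cox models follow.
- **Statistical methods, closing sentence of the same paragraph.** "The inter-eye correlation will be adjusted for all analyses including both eyes from the same subject".
- **Abstract, Methods.** Chi-square or Fisher is assigned to the primary outcome, and "mixed model and generalized estimated equation (GEE) model for the secondary outcome".
- **Sample size.** The glaucoma calculation is for Fisher's exact test in eyes, "to achieve 90% power with a two-sided alpha of 0.0492", with "the interim analysis at 6 months postoperatively spending alpha of 0.0054". It assumes 75% bilateral children, the same surgery in both eyes, and "inter-eye correlation among bilateral patients = 0.5".

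**The concern.** The glaucoma outcome is one of two primary outcomes. Because both eyes of a bilateral child are in the same arm, positive correlation between them makes the between-arm difference more variable than the same number of independent eyes would. A standard chi-square, Fisher or log-rank test on eyes ignores this and tends to give p-values that are too small.

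The sample size section discounts the second eye by dividing by 1 + 0.5. A standard test on eyes would count it in full. An analyst could follow the sentence naming the test or the sentence promising adjustment, get different p-values, and claim to have followed the protocol either way. What is at stake is whether the stated levels of 0.0492 and 0.0054 are the levels actually used.

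**Working it through.** **Inputs (Sample size section).** Event rates 12% and 0.7%; two-sided alpha 0.0492 final and 0.0054 interim; power 90%; loss 20%; 75% bilateral; correlation ρ = 0.5; both eyes in the same arm.

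**1. The plan's own figures.**
- The two-proportion formula with pooled variance gives 97 eyes per group; with the continuity correction it gives 114, the stated number.
- Loss: 114/0.8 = 142.5, so 143.
- Children: X = 143/(0.75 × 2/1.5 + 0.25) = 143/1.25 = 114.4, stated as 114.

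The stated figures reproduce, and the number of children already allows for the correlation.

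**2. Eyes in the analysis.** 114 × 1.75 = 199.5 eyes per arm. After 20% loss, 114 × 0.8 = 91.2 children and 159.6 eyes per arm.

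**3. Design effect for a standard test on eyes.** DE = [0.25 + 0.75 × 2 × (1 + ρ)]/1.75. At ρ = 0.5: (0.25 + 2.25)/1.75 = 1.43.

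**4. Large-sample level of the unadjusted chi-square test.** Level = 2 × [1 − Φ(z/√DE)], with √1.43 = 1.195.
- Final look: z = 1.967; 1.967/1.195 = 1.646; level 0.0998.
- Interim look: z = 2.782; 2.782/1.195 = 2.328; level about 0.020.

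**5. Simulation under the null** (60,000 replicates per setting; 91 and 114 children per arm; nominal 0.0492; ρ = 0.5). The null rate of 6.35% is the mean of 12% and 0.7%.

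| Test on eyes | Null rate 6.35-12% | Null rate 3% |
|---|---|---|
| Chi-square, unadjusted | 9.7-10.2% | 9.4-10.1% |
| Fisher, unadjusted | 6.5-7.9% | 5.0-5.8% |
| Cluster-robust score test | 4.7-4.9% | 4.2-4.6% |

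With ρ = 0 the unadjusted chi-square level was 4.6-5.1%, so the excess comes from the pairing.

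**6. Sensitivity to ρ**, over null rates 3-12%:
- ρ = 0.3: chi-square 7.3-8.2%, Fisher 3.6-6.2%.
- ρ = 0.7: chi-square 11.9-12.3%, Fisher 6.7-9.8%.

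**7. Which of the two named tests would be used?** At a 6.35% rate, expected events per arm are 0.0635 × 159.6 = 10.1 to 0.0635 × 199.5 = 12.7. The usual small-count reason for Fisher would then not arise, and chi-square is the likelier choice. At a 3% rate, using Fisher only when the expected count is below 5 gave 7.1% and 8.9% (91 and 114 children per arm).

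**8. Log-rank.** A smaller simulation on eyes (6,000 replicates, rate 6.35%, 114 children per arm, 20% loss) gave 0.104. It was not cross-checked, and the verdict does not rest on it.

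**9. Power of valid alternatives** at 12% against 0.7%, 91 children per arm, ρ = 0.5: about 0.98 for a clustered score test and 0.97 for Fisher's test on one record per child. The child-level Fisher test has a type I error of about 0.026-0.032.

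**The case against.** A reader might infer that the trial's false-positive rate is 7-10%. The documents do not support that. The closing sentence of Statistical methods comes after the chi-square, Fisher, log-rank and Cox sentences and exempts none of them. The inflation arises only if that sentence is not acted on.

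A reader might also say that the named tests cannot accommodate the correlation at all. That is too strong: cluster-adjusted chi-square tests and robust log-rank tests exist. Only Fisher's exact test on eyes lacks a ready adjusted form.

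Three further points have weight.
- The section does not state the unit for this test. The eye is inferred from the Sample size section, which sizes the same test in eyes. A test per child would not be inflated by pairing, but the article does not specify one.
- The GEE sentence in Statistical methods is not limited to secondary outcomes. However, the next sentence names a different test for the primary outcome, and the abstract makes the same split.
- How an adjustment is implemented is commonly left to the analysis plan. That is fair for the choice between, say, GEE and a Rao-Scott test. It does not cover this case, because the article fixes a specific test that in standard form conflicts with its own rule.

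Nor is the trial shown to be too small on this account: the number of children already discounts second eyes.

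**Conclusion.** The point holds in conditional form. The article assigns standard independent-unit tests to a primary outcome sized in paired eyes, promises an adjustment that those tests do not make in standard form, and does not say how the two fit together.

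Run unadjusted on eyes at the protocol's ρ = 0.5, chi-square would have a level of about 10% against 4.92%, and about 0.020 against 0.0054 at the interim look. Fisher would be at about 6.5-8% for null rates of 6.35-12%, and near nominal at a 3% null rate or at lower correlation. With the adjustment applied, the level is at or below about 4.9%.

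These figures rest on the eye as the unit, on the assumed 75% bilateral share and correlation, and on the null rates shown. The correlation is a planning value, and the size of the excess moves with it. The conflict between the sentences does not depend on any of these figures.

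**What to change.** In Statistical methods, replace the chi-square/Fisher sentence with one prespecified primary method for the 1-year comparison on eyes, clustered by child: a GEE or cluster-robust score test, or a Rao-Scott chi-square. State the unit and use the same method at the interim and final looks.

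A Fisher test on one record per child (event in any study eye) can be a prespecified sensitivity analysis. It should not be a fallback triggered by the observed counts, since that would let the data change both the unit and the quantity compared.

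Specify cluster-robust versions of the log-rank test and the Cox model, and amend the abstract to match.

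The cost is a few sentences, a few lines of code and a somewhat larger p-value. The sample size does not change, and power at the planned effect stays above 90%.

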### Study setting

This study will be carried out in four eye clinics across China, including (1) Zhongshan Ophthalmic Center (ZOC), Sun Yat-sen University; (2) Hainan Eye Hospital, Zhongshan Ophthalmic Center, Sun Yat-sen University (HNZOC); (3) the First Affiliated Hospital of Guangxi Medical University; and (4) Shenzhen Eye Hospital.

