### Randomization

Stratified block randomization will be applied for this trial. The eligible participants stratified by site who consented will then be divided into two strata according to secondary intraocular lens implantation in the unilateral eyes or bilateral eyes. Participants in each stratum will be randomized (1:1) to receive the assigned treatment from either secondary in-the-bag IOL implantation or secondary sulcus IOL implantation. An independent statistician without involvement in the study will generate the randomization sequence for each stratum using an online randomization number generator (http://www.randomization.com).Study participants with one study eye will be randomly assigned to one of the treatment groups.Study participants with two study eyes (both eyes are eligible):If capsular surgery is applicable for both eyes, study participants will be randomly assigned to one of the treatment groups, and both eyes will receive the same treatment.If capsular surgery is applicable for only one eye, which will be randomly assigned to one of the treatment groups, the contralateral eye will receive sulcus surgery or other appropriate treatment.

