#### History information

The following patient information will be collected: sex, age at secondary IOL implantation, age at the cataract extraction, laterality of IOL implantation, operation interval, systemic and ocular history, ocular and systemic comorbidities, and eye symptoms.

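### The adjusted Cox model pre-specifies laterality but not site, although allocation is stratified by both, and a univariable P < 0.20 screen decides whether site and the other covariates enter

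*Protocol article*

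**What the plan says.** **Randomization.** Allocation uses stratified blocks: "The eligible participants stratified by site who consented will then be divided into two strata". Within each site, the split is made "according to secondary intraocular lens implantation in the unilateral eyes or bilateral eyes". There are therefore two stratification factors. Study setting gives the number of levels of the first: "This study will be carried out in four eye clinics across China".

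**Statistical methods.** Unadjusted and adjusted hazard ratios for glaucoma-related adverse events "will be estimated by univariable and multivariable Cox proportional hazards model, respectively". The content of the multivariable model is then fixed: "Study group, stratification variable (laterality), and other baseline variables with" P below 0.20 "in the univariable analysis will be included in the multivariable model". Laterality is the only stratification variable named. Site is neither named nor ruled out. No list of the other covariates is given.

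**History information.** The variables collected at entry include "sex, age at secondary IOL implantation, age at the cataract extraction, laterality of IOL implantation, operation interval", followed by ocular and systemic history, comorbidities and eye symptoms. Ocular measurements at baseline add further candidates.

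The same part of Statistical methods compares the 1-year incidence of glaucoma-related events, one of the two primary outcomes, with a chi-square or Fisher test. The screened Cox model sits beside that test, together with Kaplan–Meier curves, a log-rank test and an unadjusted hazard ratio.

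**The concern.** An article may leave its covariates to the analysis plan. This one does not: it states a rule, and the rule does not match the design it reports. Two questions follow.

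1. A factor used to stratify allocation is normally carried into an adjusted analysis by design. Here laterality is treated that way and site is not. Whether site is adjusted for depends on a P value seen only after the outcomes are in.
2. The remaining covariates are chosen by their association with the outcome in the trial's own data. The model is then fitted and its 95% interval reported as if it had been chosen in advance. With few events, chance associations largely decide which variables pass.

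What is at stake is how credible and reproducible the adjusted hazard ratio is. The Background presents missing adjustment for important determinants of adverse events as a gap in the existing evidence, so readers are likely to give this estimate weight.

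**Working it through.** **Inputs (Sample size section, unless noted).** One-year incidence 12% with sulcus and 0.7% with in-the-bag implantation; two-sided alpha 0.0492; power 90%; loss 20%; 75% bilateral; inter-eye correlation 0.5; 228 patients; four sites (Study setting).

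**1. Reproduce the plan's figure.** Two-proportion formula with pooled null variance, difference 0.12 − 0.007 = 0.113, mean proportion 0.0635:

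n = [1.967 × √(2 × 0.0635 × 0.9365) + 1.282 × √(0.12 × 0.88 + 0.007 × 0.993)]² / 0.113² ≈ 96.2, so 97 per group.

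With the continuity correction this becomes 114, the stated number. Then 114 / 0.80 = 142.5, so 143 eyes, and 143 / (0.75 × 2/1.5 + 0.25) = 143 / 1.25 = 114.4, stated as 114 patients per group. The inputs are therefore being read as the plan intends.

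**2. Expected events by 1 year.** Events = eyes per arm × (0.12 + 0.007). The plan states no event count, so four denominators are shown.

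| Denominator | Eyes per arm | Sulcus | Capsular | Total |
|---|---|---|---|---|
| Stated requirement before allowance for loss | 114 | 13.7 | 0.8 | 14.5 |
| Stated requirement with allowance for loss | 143 | 17.2 | 1.0 | 18.2 |
| Actual eyes less 20%: 228 × 1.75 × 0.8 / 2 | 159.6 | 19.2 | 1.1 | 20.3 |
| Actual eyes, no loss: 228 × 1.75 / 2 | 199.5 | 23.9 | 1.4 | 25.3 |

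The central figure is about 20 and the range is 14 to 25. These are eyes. Fellow eyes are correlated, so the information is less than the same number of independent events would give.

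**3. What a P < 0.20 screen does with that many events.**

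- *A variable with no association* enters with probability 0.20. Leaving out laterality, which is forced in, History information lists about seven other items. The expected number of chance entries is 7 × 0.20 = 1.4, and the probability of at least one is 1 − 0.8⁷ = 79% if the items were independent.
- *A variable that does matter* can be missed. Assume a hazard ratio of 1.5 per standard deviation (not from the documents). The Wald statistic is about ln(1.5) × √20.3 = 1.83, against a threshold of 1.28, so the variable passes about 71% of the time. The range is 61% at 14.5 events to 78% at 25.3. With an assumed ratio of 1.3 the range is 40% to 52%; with 2.0 it is 91% to 99%.

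Both errors are common enough that the selected set would often differ on repetition of the trial. The same lottery applies to site: if it is unrelated to outcome it enters one time in five, and if it is moderately related it may still be left out.

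**4. Room in the model for site.** Study group and laterality use two coefficients: 14.5/2 = 7.2 to 25.3/2 = 12.7 events per coefficient. Site as a factor adds three: 14.5/5 = 2.9 to 25.3/5 = 5.1. Stratifying the Cox model by site adds none.

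**5. A limit that covariates do not change.** The chance of no event in the capsular arm by 1 year is 0.993ⁿ: 45% for n = 114, 33% for n = 159.6 and 25% for n = 199.5, treating eyes as independent. In that case an ordinary Cox hazard ratio cannot be estimated at 1 year, whatever is adjusted for.

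**The case against.** The strongest reply is that little depends on this model. The screening rule is attached only to the multivariable Cox analysis. The 1-year glaucoma comparison rests on a chi-square or Fisher test, decentration on a mixed model without that rule, and the unadjusted hazard ratio and log-rank test appear beside the adjusted estimate. This stands, and it limits the point to a supporting analysis.

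Three further replies also stand.

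- *Site is not excluded.* It can come in as one of the other baseline variables. The fault is that it is not pre-specified.
- *Twenty events is a 1-year count.* The Cox and Kaplan–Meier analyses carry no 1-year limit, and follow-up runs to 10 years. Later analyses would have more events and a steadier screen; how much steadier cannot be said, because no later rate is given.
- *Chance entry of a baseline covariate does not by itself bias a randomised comparison.* The 79% above describes instability of the model, not error in the hazard ratio.

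What the reply does not remove is the mismatch between two stated passages, or an interval that ignores how its model was chosen.

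A reader might also infer things the document does not support. It does not say that site determines the surgeon or the measuring device. The term operation interval is not defined, so exact collinearity with the two ages is conjecture; if it were so, dropping the redundant term would leave the treatment coefficient unchanged. The mixed and GEE models are described without covariates, and in a condensed article that silence is no finding.

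**Conclusion.** The point holds for the adjusted Cox model. Allocation is stratified by site and laterality; the model guarantees only laterality and leaves site to a screen on the trial's own outcomes. At 1 year, with about 20 events (14 to 25) and about one in the capsular arm, that screen gives an unstable covariate set and an interval that does not reflect the selection.

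It would be tempting to conclude that leaving out site inflates the false-positive rate or undermines the primary result. Neither follows. Ignoring a prognostic stratification factor generally makes inference conservative and loses efficiency, and the primary test does not use this model. If site is not prognostic, little is lost.

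The event figures assume the protocol's own 1-year rates. The miss rates assume the illustrative hazard ratios shown, and the chance-entry figure assumes independent candidates. No effect on the hazard ratio or its standard error has been calculated, because the documents give no between-site variation. This is a modest point that is cheap to correct.

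**What to change.** In Statistical methods:

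1. Name both site and laterality as stratification variables, in agreement with Randomization.
2. Stratify the Cox model and the log-rank test by site, pooling very small sites by a rule stated in advance, and keep laterality as a covariate in the Cox model. Stratifying is preferable to three site coefficients, given the counts above.
3. Delete the P < 0.20 rule. Replace it with a short list of baseline covariates already collected, for example age at secondary implantation, fixed before outcome data are examined, including those for the planned 6-month interim analysis. With study group, laterality and one such covariate, the model has three coefficients, or 14.5/3 = 4.8 to 25.3/3 = 8.4 events each at 1 year, so the list must stay short.

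The cost is about two sentences of text, with no new data and no change in sample size. Site strata with few or no events contribute little or nothing, so a small amount of information is lost, and the analysts give up data-driven choice of covariates. The change does not cure the sparse capsular arm at 1 year.
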